## Abstract

**Introduction:**

Pulmonary Rehabilitation (PR) is an evidence-based intervention that has been recommended in guidelines to be available to those who may benefit. However, not all patients with chronic obstructive pulmonary disease (COPD) have access to this service. Healthcare services have shown the need for the provision of PR in other forms to enable patient choice and service capacity. There is an increase in evidence for the use of the internet in the management of long-term conditions to provide education and promote self-management. The aim of this study is to see if an interactive web-based PR programme is a feasible alternative compared with conventional PR.

**Methods and analysis:**

This is a feasibility study designed to evaluate the efficacy of providing a web-based PR programme to improve patients exercise capacity, quality of life and promote self-management in patients with moderate to severe COPD compared with conventional PR programmes. Eligible patients will be randomly allocated to receive either the web-based programme or conventional rehabilitation programme for 7 weeks using an internet-based randomisation system. Participants will be recruited from PR assessments, primary care and community rehabilitation programmes. Those randomised to the web-based programme work through the website which contains all the information that the patients receive in the PR classes. They receive weekly phone calls by a professional to help progress through the course on line. The outcome measures will be recruitment rates and eligibility as well as that standard for a PR assessment including measures of exercise capacity, quality of life questionnaires and physical activity.

**Ethics and dissemination:**

The research ethics committee for Northampton has provided ethical approval for the conduct of the study. The results of the study will be disseminated through appropriate conference presentations and peer reviewed journals.

**Trial registration number:**

ISRCTN03142263.

Strengths and limitations of this studyThe study concentrates on the feasibility of an interactive web-based Pulmonary Rehabilitation (PR) programme (SPACE: Self-management Program of Activity, Coping and Education for chronic obstructive pulmonary disease). It will provide data on recruitment to enable an accurate estimation of sample size for a planned randomised controlled trial.Much of the success depends on the eligibility of the patients, that is, web literacy and access to the internet.The study will compare a variety of clinical outcomes between a web-based and a conventional rehabilitation PR programme in order to test the various components of the intervention.

## Introduction

It is estimated that one in four people will develop chronic obstructive pulmonary disease (COPD) in their lifetime^1^ and it is the fourth leading cause of death in the UK. COPD is characterised by a progressive deterioration of debilitating symptoms and increasingly frequent exacerbations. Pulmonary Rehabilitation (PR) has been proven to be effective in improving quality of life, psychological functioning and physical activity and national guidelines recommend that PR should be available to all those who may benefit.^2^ However a survey by the British Lung foundation has found that fewer than 10% of people with COPD have access to such a service.^3^

The standard provision of PR is a supervised package of exercise and education, usually twice a week for a minimum of 6 weeks supported by a home exercise programme. However, some patients find visiting a hospital or community facility very difficult and many programmes report dropout rates as high as 50%. A web-based PR programme has the potential to be a novel and effective approach to increasing patient choice in the mode of delivery and setting of rehabilitation (especially to those patients who decline the offer of conventional PR) while simultaneously increasing the capacity of PR.

There is a growing evidence base for the use of the internet in the management of many chronic conditions in areas as diverse as the management of diabetes, Parkinson's disease, depression, rheumatoid arthritis, asthma, chronic pain and epilepsy.^4–10^ In COPD, Nguyen *et al*^11^ published pilot data on an online dyspnoea self-management programme which had comparable outcomes to a face to face programme but was stopped early due to multiple technical challenges with the online programme.

Our institution has recently pioneered the development of ‘ACTIVATE ***YOUR*** HEART’ (AYH)^12^ which is an interactive web-based cardiac rehabilitation (CR) programme and has proved very popular with patients, with the recruitment of 80 patients far exceeding the initial target of 25. Brough *et al* (2014) reported a significant improvement in exercise capacity and quality of life in patients that completed the web-based programme. Following the success of AYH, we have developed a prototype website based on the educational content of the ‘SPACE for COPD’ self-management workbook. SPACE (Self-management programme of Activity, Coping and Education) for COPD 13 is a structured programme of exercise, education and psychosocial support which has been developed by our institution as a collaboration between experts, patients and carers and has been awarded a Crystal Mark for Clarity by the Plain English Campaign.

The aim of this feasibility study therefore is to provide quantitative, qualitative, economic and technical data which will inform and refine the subsequent design of a randomised controlled trial (RCT) which will compare web-based and conventional PR across a range of clinical and health economic outcomes.

The objectives for the study are:
To gather information regarding the recruitment rate of patients who are eligible and willing to be randomised to either the web-based or the conventional rehabilitation programme, and to monitor retention and drop out through all stages of the programmes.To perform a pilot study which will compare a variety of clinical outcomes between an web-based and a conventional rehabilitation PR programme in order to test out the various components of the intervention and identify any technical or other difficulties that may be inherent in the delivery of an web-based PR programme.To collect data regarding the primary outcome measure (change in exercise capacity as measured by the incremental shuttle walking test) which will allow a calculation of sample size to be estimated in the eventual trial.To explore patients’ experiences of participating in the rehabilitation programmes in order to identify barriers and facilitators to recruitment and retention in the subsequent RCT and to identify any further changes needed in the design of the website.To design and pilot a suitable patient cost questionnaire to be used in the proposed cost-effectiveness economic evaluation in the subsequent RCT.

## Methods and analysis

### Trial design and registration

This is a feasibility study to inform the design of a RCT. Patients are randomised to either conventional rehabilitation programme as is standard at their referred site or the web-based PR programme (SPACE for COPD).

The trial is registered on the ISRCTN website. The trial was registered prospectively by the local CLRN. The final authorisation came through the day after the first patient had been recruited.

### Participants

#### Eligibility criteria for participants

Eligible participants are those with an established diagnosis of COPD defined as a forced expiratory volume in 1 s (FEV1), post-bronchodilation of <80% and a predicted ratio of FEV1 to forced vital capacity of 0.70 and a Medical Research Council (MRC) dyspnoea score of between 2 and 5. Patients must be willing to partake in either arm of the study. Access to the internet for more than 3 months, the ability to navigate around a variety of websites (eg, uses online shopping or banking websites) and regularly use email is required. Patients must also be able to read and write in English.

Patients are excluded from participating in the trial if they are unable to participate in the exercise component of the rehabilitation programme due to other comorbidities. Eligible patients must be willing and able to take part in the web-based programme. Participation in PR in the previous 12 months would also exclude the patient.

#### Setting

Participants to the study will be primarily recruited from those patients that have been referred for PR at University Hospitals of Leicester (UHL) NHS Trust. Recruitment will also be directly from primary care and Rehabilitation services within Leicester Partnership Trust (LPT). All potentially suitable participants will receive a patient information sheet about the study, an invitation letter on behalf of the study team as well as their initial letter confirming their referral to PR, as is standard for the LPT service. Potentially eligible participants will also be identified from the research participant database of the Leicester Respiratory Biomedical Research Unit and PR Database.

### Trial interventions

#### Intervention development

A preprotocol award from the NIHR East Midlands Research Design Service (RDS) enabled us to conduct a focus group with current and ex-PR patients to gain feedback on the prototype website, with particular regard to features that increase interactivity and usability for service users as well as addressing any concerns such as data security. The model for the interactive web-based PR programme has been based on recent, similar work by our institution on the ‘ACTIVATE ***YOUR*** HEART’ web-based CR programme and the previously successful SPACE manual.^13^ Three patients who took part in AYH also took part in the focus group. Information from the focus group has enabled the project team to work with the web-designers to ensure that the final design of the website is in line with these preferences, ideas and feedback. The website has undergone practical ‘road-testing’ by members of the focus group and other members of the departmental patient and public involvement (PPI) group to ensure that participants can access the website and navigate easily around the site.

#### Intervention group—web-based PR programme

Following randomisation to the intervention group, patients will be given an appointment to attend an initial session that will introduce the web-based PR programme. At this initial session, the website will be introduced by a PR specialist who is trained in the techniques of motivational interviewing as well as being an expert in PR. Participants will be given a password protected secure login to the website as well as written instructions on website navigation.

The rehabilitation specialist will signpost the patient to all the relevant sections on the website for getting started with the programme as well as going through the home exercise programme and goal setting. There is also an individualised webpage featuring a personalised action plan designed to assist in the management of exacerbations which will be completed by the rehabilitation specialist in conjunction with the patient.

As in conventional PR, patients will be encouraged to exercise on a daily basis at home and record their progress in the online exercise diary section. Throughout the duration of the web-based programme the rehabilitation specialist will be able to review the patient's progress online and communicate with the patient via email or telephone depending on patient preference. There will be weekly contact between the patient and the rehabilitation specialist to ensure that patients are helped to progress their exercise programme appropriately and to answer any queries that arise.

The educational content of the web-based programme is based on the ‘SPACE for COPD’ manual. Patients on the intervention arm of the study will be allowed to work through the website content at their own pace, however, certain milestones need to be completed or achieved before further content can be accessed in order to ensure appropriate progress through the programme. We anticipate from our work with a comparable CR web-based programme ‘ACTIVATE ***YOUR*** HEART’, that it will take approximately 6 weeks to work through the online programme. Patients will then be given an appointment to come into the hospital to attend a discharge appointment once they have completed the programme. The patient is offered a course of conventional rehabilitation classes if they feel it would be more beneficial.

#### Standard care group—conventional PR programme

Standard care for patients referred for PR at UHL is hospital-based rehabilitation and community-based for those referred to LPT. The PR programme at UHL has been running for nearly 20 years and is a well-established programme with a strong evidence base.^14^
^15^ Patients randomised to standard care will start conventional rehabilitation according to the standard care at their referred site on the next available date.

Conventional PR programmes consist of twice weekly sessions each lasting 2 h which are divided into an hour for exercise training and an hour for an education session covering a variety of relevant self-management topics. The exercise training consists of endurance based walking, static cycling and strength training with weights. The programme is run by PR specialists who progress people through the exercise programme as able and appropriate. Patients are encouraged to also complete a home exercise programme on the days when they do not attend rehabilitation classes and to fill in an exercise diary. The educational sessions are conducted as group sessions and delivered by experts in their field. There is plenty of opportunity for discussion as well as questions and answers and the topics covered include medication, relaxation skills, chest clearance and breathlessness management and energy conservation.

During the period of their rehabilitation patients are given a telephone number so they can contact a member of their rehabilitation team if they have any queries or concerns.

After completing the conventional rehabilitation sessions patients will be given an appointment to attend a discharge assessment (usually approximately 6–7 weeks after starting the programme) as is standard for their rehabilitation service.

At the end of the discharge assessment all patients will be given advice on continuing their home exercise programme, regardless of group allocation.

### Outcome measures

#### Clinical measures

All the measures described below are routinely included in the clinical evaluation of our standard PR programme, with the exception of the use of activity monitors. All measures (except for activity monitors) will be completed at the time of initial assessment for PR by members of the rehabilitation team or at the consent appointment by the research team both who are experienced in these measures. The PR assessment includes information on medical history, medication and baseline demographic data. Standard measures of lung function, level of physical activity, exercise capacity, information needs and health status will be collected.

All measures will be repeated again at the discharge assessment following completion of either rehabilitation programme (usually approximately 6–7 weeks after starting the programme) and will be conducted by a research physiotherapist who will be blind to treatment group allocation.

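### Follow-up outcomes are booked on programme completion, so the ISWT data passed to the RCT would describe completers only

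*Protocol article*

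**What the plan says.** All references are to the protocol article.

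- **Trigger, both arms** (Clinical measures): "All measures will be repeated again at the discharge assessment following completion of either rehabilitation programme". The nominal timing follows and covers both programmes: "usually approximately 6–7 weeks after starting the programme) and will be conducted by a research physiotherapist".
- **Trigger, web arm** (Intervention group): "Patients will then be given an appointment to come into the hospital to attend a discharge appointment once they have completed the programme".
- **Trigger, conventional arm** (Standard care group): "After completing the conventional rehabilitation sessions patients will be given an appointment to attend a discharge assessment".
- **Measures that depend on the same visit.** Questionnaires go out a week before the discharge appointment (Questionnaires). The cost questionnaire goes out before it (Patient cost questionnaire). The activity monitor and the PACER questionnaire come after it (Physical activity; Physical activity questionnaire).
- **Pace, web arm:** "Patients on the intervention arm of the study will be allowed to work through the website content at their own pace", with milestones that unlock later content. The expectation is that "it will take approximately 6 weeks to work through the online programme". No maximum is given.
- **Length in the abstract:** patients are allocated "to receive either the web-based programme or conventional rehabilitation programme for 7 weeks".
- **Non-completers** (Uptake and drop out): starters, completers and dropouts are counted in both groups. Time to complete the web programme is recorded, and for dropouts, how soon they left and how much they had done. No outcome visit is mentioned.
- **Use of the data:** ISWT change is to give the RCT sample size (Primary outcome measure) and the non-inferiority margin (Quantitative data analysis).

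**The concern.** Completing the programme happens after randomisation and may be related to how well a patient is doing. If only completers reach the follow-up walk test, the arm summaries no longer describe the groups that were randomised, and the two arms may be selected differently.

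The descriptive analysis does not remove the problem, because the descriptive means and SDs are what this study hands to the RCT. The same condition applies to the EQ-5D-5L and cost questionnaire response rates that the health economic section wants to examine. The design also merges two events that an RCT team needs to separate: stopping the programme and being lost to follow-up. Whether patients who stop will still attend a walk test is a central feasibility question, and this plan would not answer it.

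Self-pacing adds a further difficulty. With no end point, a slow web user is neither clearly a completer nor clearly a dropout, so the web completion rate depends on when counting stops.

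**Working it through.** **1. Is the trigger stated or only inferred?** Three sections (Clinical measures and the two arm descriptions) each place the assessment after completion. The one section that says what is recorded for dropouts lists timing and amount completed, and no walk test. The trigger is therefore stated. That non-completers go unmeasured is the direct reading of it.

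**2. Is there a figure of the plan's own to reproduce?** No. The figure of around 100 patients is a recruitment forecast from service experience. The article gives no SD, effect size, alpha, power or margin.

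**3. How many would have a follow-up ISWT?** The inputs are 100 recruited (Sample size estimation and recruitment target), 1:1 allocation (Randomisation), and dropout d. The 20% and 30% are assumed. The 50% is the upper end of the Introduction's remark that "many programmes report dropout rates as high as 50" per cent.

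Number measured = 100 × (1 − d):
- d = 20%: 80 (40 per arm)
- d = 30%: 70 (35 per arm)
- d = 50%: 50 (25 per arm)

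**4. Precision of the SD.** The 95% limits for a pooled SD, as multiples of the estimate, are √(df/χ²₀.₉₇₅) and √(df/χ²₀.₀₂₅), with df = N − 2. Sample size scales with the SD squared.

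| Measured | SD limits | RCT sample size limits |
|---|---|---|
| 100 | 0.88 to 1.16 | 0.77 to 1.35 |
| 80 | 0.87 to 1.19 | 0.75 to 1.41 |
| 70 | 0.86 to 1.20 | 0.73 to 1.44 |
| 50 | 0.83 to 1.25 | 0.70 to 1.56 |

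**5. Selection, as an illustration only.** Suppose completion depends on a latent normal variable with correlation r to ISWT change. Put c = z(d) and λ = φ(c)/(1 − d). Completers' mean is then shifted by rλ SD, and their variance is multiplied by 1 − r²λ(λ − c). Nothing in the article supplies r; values of 0, 0.3 and 0.5 are assumed.

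At d = 50%, c = 0 and λ = 0.399/0.5 = 0.798:
- r = 0.3: shift 0.3 × 0.798 = 0.24 SD; variance ratio 1 − 0.09 × 0.637 = 0.943
- r = 0.5: shift 0.5 × 0.798 = 0.40 SD; variance ratio 1 − 0.25 × 0.637 = 0.841

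At d = 20%, the shifts are 0.11 and 0.18 SD and the variance ratios 0.962 and 0.896. At r = 0, there is no shift and no loss of variance at any d.

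An RCT sample size built on the completers' SD would be too small by about 4–10% at 20% dropout and 6–16% at 50%. If dropout were 50% in one arm and 20% in the other (assumed, with the same r in both), the between-arm difference in means would be off by 0.239 − 0.105 = 0.13 SD to 0.399 − 0.175 = 0.22 SD.

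**6. Timing.** The article gives about 6 weeks expected for the web content, 6–7 weeks to discharge in either programme, and 7 weeks in the abstract. These are nominal values without a spread, so no timing difference can be computed.

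**The case against.** A reader might infer stronger claims, and the article does not support them.

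- **That the arms are measured at different times.** Clinical measures gives one nominal 6–7 weeks from start for either programme. Drift in the web arm is a risk created by self-pacing without a maximum; it is not a stated feature of the design.
- **That the three durations contradict each other.** They are loosely compatible: an expected time through the website, a usual time to discharge, and a rounded length in the abstract.
- **That retention is known only for completers.** Uptake and drop out counts starters, completers and dropouts in both groups and records time to completion in the web arm.
- **That half the patients will be lost, or that the bias can be put in metres.** The 50% is background about other programmes, and every other input to such a figure would have to be invented.

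Other points for the plan carry some weight. An article condenses a fuller protocol, no sentence forbids assessing dropouts, completion is not defined, and interviews with dropouts are planned where possible. Yet a positively stated trigger is not a detail left out: a fuller document that followed up everyone would conflict with this text.

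The analysis is descriptive and disclaims power for between-group changes, so no test is invalidated. The SD distortion in the illustration is also smaller than ordinary sampling error, since sample size limits are 0.77 to 1.35 even with full follow-up. Both points stand and limit the severity. Finally, completer data are informative for a non-inferiority RCT, which is a reason to keep them alongside the randomised groups.

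**Conclusion.** The concern holds for the completion trigger. As written, follow-up ISWT, the endurance walk test and the questionnaires are obtained from completers in both arms, and the summaries meant to size the RCT and set its margin would describe that selected group. The study would not show whether non-completers can be followed up. On timing, the supported statement is narrower: there is no common window and no maximum in the web arm, so timing may drift between arms and the web completion rate depends on when counting stops.

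The size of any bias cannot be derived from the documents. The firmest arithmetic is that 80, 70 or 50 of about 100 patients would have a follow-up ISWT at assumed dropout of 20%, 30% or 50%. The selection figures rest wholly on assumed correlations and vanish if completion is unrelated to ISWT change; the loss of precision remains in that case. The point deserves action because follow-up that is not collected cannot be recovered later.

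**What to change.** 1. Separate the research outcome visit from completion. Invite every randomised patient, whatever they have completed, to the ISWT and endurance walk assessment already planned, in one common window counted from the same origin in both arms. Record the wait from randomisation to programme start, since conventional care begins on the next available date.
2. Send the questionnaires to all patients before that window, including those who have stopped.
3. Summarise outcomes as randomised, with completers as a secondary description. Report separately how many non-completers attended.
4. Count web completion as of the end of the window, and go on recording time to completion.
5. Align the 6, 6–7 and 7 week statements with the window, so that one timing is stated throughout.

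**Cost.** The change needs protocol wording, a fixed booking date, and some visits and postage for non-completers. At the assumed dropout rates, that is at most 100 − 80 = 20 to 100 − 50 = 50 further visits, and fewer if some decline. No new staff role or procedure is needed. Some web patients would be assessed before finishing the content, which can be reported.
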